#### Exclusion criteria

Contraindication for one of the treatment modalities, e.g. severe side effects of DA treatment or DA-resistant prolactinomaContraindications to surgery, or a clear indication for surgical resectionPregnancy at the time of randomisationClinical diagnosis of acromegalyPrior radiotherapy of the pituitary gland areaSevere renal failure (eGFR < 30 ml/min)Insufficient understanding of the Dutch and English language

Patients eligible for participation in one of the RCTs, but do not consent to randomisation because there is a clear patient preference for either DA treatment or surgery, are considered for participation in PRolaCT-O, also see Fig. 1.

**Fig. 1 Fig1:**
[figure not shown]
Overview of patient recruitment and treatment allocation

All prolactinoma patients are screened for eligibility to participate with one of the RCTs. Patients who decline randomisation or have a strong treatment preference are approached for PRolaCT-O. All ineligible patients will be approached for ProlaC, an additional registry including all prolactinoma patients (e.g. invasive tumours, pregnant patients).

### Patient identification and enrolment

Eligible patients are discussed within a regional multidisciplinary network, operating from the participating neurosurgical expertise centres. RCT eligibility is confirmed by the regional MDT. The counselling of new, eligible patients will be performed in the following order: first, willingness to participate in the RCT (PRolaCT-1, 2, 3) will be assessed, followed by willingness to be included in the intensive observational cohort with shared decision-making (PRolaCT-O). Patients who fulfil RCT eligibility but do not consent to randomisation or have a clear preference for standard care (PRolaCT-1) or either treatment modality (PRolaCT-2 and PRolaCT-3) are approached for participation in the observational arm, PRolaCT-O, which is depicted in Fig. 1. Patients who were approached for PRolaCT-1, but do not participate with PRolaCT, may be approached again for participation in PRolaCT-2 or PRolaCT-3, when the duration of DA treatment fulfils the inclusion criteria of the respective RCT. Likewise, patients who are enrolled in PRolaCT-O and receive standard care may be approached for participation in PRolaCT-2 or PRolaCT-3 if they reconsider surgical treatment. Written informed consent will be obtained from all participants prior to study inclusion.

### Treatment allocation

Within each RCT (PRolaCT-1, PRolaCT-2, or PRolaCT-3), participants are randomly allocated in a 1:1 ratio to either neurosurgical counselling (with potential subsequent surgery when desired) or standard care with DA. Randomisation is performed in blocks of sizes varying between 4, 6, and 8 patients and is stratified by sex to equally divide male participants and by tumour size (< 10 mm versus ≥ 10 mm). Randomisation is performed centrally in the LUMC using the built-in randomisation tool of the web-based database programme (Castor Electronic Data Capture (EDC), Castor, Amsterdam, the Netherlands). Investigators, treating physicians, and participants will not be blinded to the outcomes of randomization. With the use of varying block sizes, the allocation sequence is kept concealed by the randomisation programme. In PRolaCT-O, treatment choice, based on patient and physician preference, is solely recorded and may be DA treatment as a first- or second-line treatment, or surgical counselling as a second-line treatment (thus not in newly diagnosed patients). For all studies, the interpreters of MRIs, ophthalmologic assessments, and surgical difficulty will be blinded when possible. Unblinding will not occur.

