## Methods

### Study design

This combined randomised clinical trial and observational cohort study design comprises three unblinded parallel superiority prolactinoma RCTs (PRolaCT-1, PRolaCT-2, PRolaCT-3) and an observational study arm (PRolaCT-O) that will compare counselling for endoscopic transsphenoidal adenoma resection to standard care (DA treatment) in patients with a prolactinoma of limited size (i.e. < 25 mm, no tissue invasion):
PRolaCT-1 compares counselling for surgical resection as a first-line treatment in newly diagnosed, treatment-naïve prolactinoma patients.PRolaCT-2 compares counselling for surgical resection as an early second-line treatment in patients who have had DA treatment for a limited time period (4–6 months).PRolaCT-3 compares counselling for surgical resection as an equal second-line treatment in patients who have persisting prolactinoma, i.e. recurring hyperprolactinaemia and persisting pituitary adenoma on MRI, after DA treatment for a long period of time (> 2 years).PRolaCT-O evaluates counselling for surgical resection as an equally valid second-line treatment and standard care in an observational study setting, aiming to include all patients eligible for PRolaCT-1, PRolaCT-2, and PRolaCT-3 who do not participate in the RCTs because of a strong patient and/or physician treatment preference, and/or because the patient does not consent to randomisation.

All interventions and study procedures are otherwise identical for the three RCTs and the observational cohort.

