### Sample size calculation

To detect a difference in remission rate at 36 months of 40% between surgery (expected rate 90%) and medical treatment (expected rate max. 50%), with a power of 0.8 and an *α* of 0.025, 55 patients per treatment group arm are needed, when considering that max. 30% in the interventional arm will not undergo surgery. However, to detect a difference of 10 points at the SF-36 mental health scale at *T* = 12 with an *α* of 0.025 and a power of 0.8, assuming that the standard deviation is 16, based on the general population [31], and that max. 30% of the interventional arm does not undergo surgery, at least 101 patients per treatment arm are needed. To compensate for the loss to follow-up, it is aimed to include 110 patients per treatment arm and therefore 220 patients in total per RCT/PRolaCT-O (aiming for at least 110 patients per treatment group in PRolaCT-O). If patient recruitment would prove challenging, and the required sample size for separate analyses of the RCTs cannot be reached for two or more of the RCTs (PRolaCT-1, PRolaCT-2, or PRolaCT-3) within the duration of the study, the planned analyses could be performed using the combined sample size for two to three RCTs of 220 patients.

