##### Analyses in PRolaCT-O using propensity score methods

As the treatment groups in PRolaCT-O may differ at baseline, propensity score methods will be used to account for potential confounding. The propensity to receive surgical counselling will be estimated using logistic regression including potential confounders such as duration and effectiveness of prior DA treatment, the amount and severity of side effects to DA treatment measured at study entrance measured with the PRO-CTCAE, age at inclusion, gender (male or female), type of centre treatment takes place (secondary or tertiary), physician enrolling the patient (endocrinologist, gynaecologist, or neurosurgeon), prolactinoma size (micro- or macroadenoma), patient and MDT treatment preference pre- and post-counselling (neutral, medication, or surgery), and the likelihood of positive surgical outcome (unlikely, possibly, or likely) as estimated post hoc by two neurosurgeons blinded to received treatment. Adequacy of the propensity model will be assessed by checking if standardised mean differences after propensity adjustment are below 0.10 and by inspecting balancing plots.

Inverse probability weighting based on the propensity score will be used to balance the treatment groups. After observations are reweighted, treatment groups are compared in the same way as in the RCTs. Propensity matching will be used as a sensitivity analysis.

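### PRolaCT-O enrols treatment-naive patients who by rule cannot receive surgical counselling there, yet its weighted comparison neither excludes them nor names a target population that would

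*Protocol article*

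**What the plan says.** **Who enters.** Study design describes PRolaCT-O as "aiming to include all patients eligible for PRolaCT-1, PRolaCT-2, and PRolaCT-3 who do not participate in the RCTs". The inclusion criteria define PRolaCT-1 by the absence of any prior prolactinoma treatment. Patient identification and enrolment gives the route in: patients who are RCT-eligible but do not consent to randomisation, or who "have a clear preference for standard care (PRolaCT-1) or either treatment modality (PRolaCT-2 and PRolaCT-3").

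**What they can receive.** Under Treatment allocation, the choice of treatment in PRolaCT-O "is solely recorded and may be DA treatment as a first- or second-line treatment". The only alternative that the section names for this cohort is worded as "or surgical counselling as a second-line treatment (thus not in newly diagnosed patients").

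**How they are compared.** The section on propensity score methods says: "The propensity to receive surgical counselling will be estimated using logistic regression including potential confounders such as duration and effectiveness of prior DA treatment", followed by other covariates. It continues: "Inverse probability weighting based on the propensity score will be used to balance the treatment groups". The groups are then compared as in the RCTs, with propensity matching as a sensitivity analysis. Adequacy is judged by whether "standardised mean differences after propensity adjustment are below 0.10 and by inspecting balancing plots". Planned statistical analyses lists PRolaCT-O as one unit of analysis beside the three RCTs, and provides for a meta-analysis of all four in any event.

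**How many.** Sample size calculation is "aiming for at least 110 patients per treatment group in PRolaCT-O".

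**The concern.** Weighting by the inverse of the propensity score needs every kind of patient in the target population to have some chance of each treatment (positivity). Here one kind of patient has no chance of counselling. This is written into the allocation rule, so more recruitment will not cure it.

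The imbalance falls on a variable that plausibly matters for both primary outcomes. PRolaCT-3-eligible patients have persisting disease after more than 2 years of DA and a withdrawal attempt; naive patients have had no such test. The baseline mental health score is an untreated score in naive patients and follows DA treatment in the others. One listed covariate, the effectiveness of prior DA treatment, has no defined value in a naive patient.

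PRolaCT-O is the stated fallback for the primary and secondary objectives. The Discussion reports that recruitment has been limited so far and expects the cohort to give results before the RCTs. A distorted contrast there would also enter the combined meta-analysis.

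**Working it through.** **1. The plan's own sample size reproduces, so it is not the fault.** Inputs from Sample size calculation: 10 points, SD 16, α 0.025 (taken as two-sided), power 0.8, 30% of the intervention arm not operated.
- HRQoL: diluted difference 10 × 0.70 = 7. n = 2(2.241 + 0.842)² × 16²/7² = 99.3, so 100 per arm; the t-test version gives 100.6, so 101, as stated.
- Remission: 0.70 × 90% + 0.30 × 50% = 78%, against 50%. The two-sided test without continuity correction gives 55 per arm, as stated.

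**2. Weighted composition.** Let q be the naive share of the PRolaCT-O cohort. The protocol gives no figure, so q is assumed throughout. Naive patients have propensity 0, hence weight 1/(1 − 0) = 1 in the DA group. With correct propensities elsewhere, pre-treated DA patients are weighted up to stand for all pre-treated patients, a share of 1 − q. The weighted naive share is therefore q/(q + 1 − q) = q in the DA group and 0 in the counselling group.

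**3. Standardised mean difference (SMD) on naive status.** SMD = q/√(q(1 − q)/2) = √(2q/(1 − q)).

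| Assumed q | SMD |
|---|---|
| 0.5% | 0.10 |
| 1% | 0.14 |
| 5% | 0.32 |
| 10% | 0.47 |
| 20% | 0.71 |
| 30% | 0.93 |
| 50% | 1.41 |

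Setting the SMD to 0.10 gives 2q/(1 − q) = 0.01, so q = 0.01/2.01 = 0.498%. Above that share the plan's limit is exceeded.

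**4. Effect on the contrast.** Let D be the mean outcome of naive DA patients minus that of pre-treated DA patients, after the plan's adjustment. The weighted DA mean is shifted by q × D, so the contrast differs from the pre-treated effect by −q × D. Neither q nor D is in the protocol, so no size or sign can be given.

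**5. Would the balance check show it?** That depends on coding. A simulation of 200,000 patients assumed counselling probabilities of 0.45 and 0.55 in PRolaCT-2- and PRolaCT-3-type patients (equal numbers), with prior DA of 5 months and of 24 to 72 months. Population-average weights gave:

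| Assumed q | Duration coding | Fitted propensity, naive | SMD, duration | SMD, naive status |
|---|---|---|---|---|
| 10% | linear | 0.361 | 0.003 | 0.606 |
| 33% | linear | 0.217 | 0.041 | 1.196 |
| 50% | linear | 0.145 | 0.091 | 1.645 |
| 10% | by class | 0 | 0.114 | 0.472 |
| 33% | by class | 0 | 0.394 | 0.990 |
| 50% | by class | 0 | 0.636 | 1.417 |

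With a linear term, the duration SMD passes while naive status is badly unbalanced. With treatment class modelled, the duration SMD does flag the problem.

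**6. Do other weights help?** In the same simulation, weights targeting the counselled patients (ATT) left a naive share of 0 in the controls when class was modelled. With the linear term they left 12.4%, 26.3% and 31.7%.

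**7. Cost of restriction.** If 30% of 110 DA patients were naive (assumed), 110 × 0.70 = 77 comparable controls remain. For 7 points, SD 16 and two-sided 0.025:
- 110 v 110: SE = 16√(2/110) = 2.157; 7/2.157 − 2.241 = 1.00; power about 84%.
- 110 v 77: SE = 16√(1/110 + 1/77) = 2.377; 7/2.377 − 2.241 = 0.70; power about 76%.

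Both are before loss to follow-up and before the variance added by weighting.

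**The case against.** The best defence is that the propensity section leaves room for a sound analysis. It names no target population, its confounder list is open, and duration of prior DA heads that list and separates naive from pre-treated patients. Study design describes counselling in PRolaCT-O as a second-line option, which fits a pre-treated target. The plan checks balance, adds matching, and foresees meta-regression if the studies differ. Choice of weights, trimming and coding are often left to a statistical analysis plan, which is not shown.

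Much of this stands as a limit on the point. A reader might infer that no weighting could ever balance the groups. The protocol does not support that: ATT or overlap weights with an explicit prior-treatment indicator, or matching within treatment class, would do so. A reader might infer that DA side effects, like prior effectiveness, cannot exist as a covariate in naive patients. But that covariate is measured at entry with the PRO-CTCAE, which can be scored in anyone. A reader might also infer that naive patients certainly count towards the 110 per group; the protocol does not say who counts. Finally, the simulated failure of the balance check rests on assumed coding and probabilities.

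The defence does not dispose of the point. The allocation rule and the analysis as written are inconsistent, which is more than detail left for later. A balance check can report the problem but does not say what to do about it. Matching is only a sensitivity analysis, and the meta-regression is conditional on results differing substantially.

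**Conclusion.** The point holds for population-average inverse probability weighting of the full PRolaCT-O cohort, the ordinary reading of the propensity section. Positivity then fails by rule. Imbalance on naive status exceeds 0.10 once about 0.5% of the cohort is naive, and is 0.47, 0.71 and 0.93 at assumed shares of 10%, 20% and 30%. These figures measure covariate imbalance, not outcome bias, whose size and direction are unknown. The existence of the violation needs only that some naive patients enrol, as the protocol intends.

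This should be fixed, but it does not threaten the trial as a whole. The RCT analyses are untouched, and the protocol itself says that the cohort cannot replace them.

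**What to change.** In the section on propensity score methods, restrict the PRolaCT-O comparison, its propensity model and its contribution to the meta-analysis to DA-pretreated patients (PRolaCT-2- and PRolaCT-3-eligible), with eligibility stratum in the model. Equivalently, name a target population that gives naive patients zero weight through an explicit prior-treatment indicator; a linear term for duration is not enough. In Sample size calculation, state that the 110 per group is counted within that set. Report naive DA patients as a descriptive cohort.

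The cost is a change of wording, fewer controls in the comparison unless recruitment makes up the number, and conclusions limited to pre-treated patients. The question of first-line counselling then rests on PRolaCT-1, since PRolaCT-O has no counselled naive patients to inform it.

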### Treatment

#### Intervention: surgical counselling

Participants who are randomised for the intervention group will receive extensive and personalised neurosurgical counselling by a neurosurgeon and an endocrinologist with specific expertise in pituitary care (preferably a combined consultation). All potential benefits and risks of surgery are discussed in a semi-standardised manner, offering both standardised information on surgical intervention and detailed expert opinion regarding the patient’s specific situation. This consultation may theoretically result in advising the patient to refrain from surgery during the shared decision-making process, despite the patient’s previous eligibility “on paper”. Moreover, based on information gathered during the counselling, the MDT may advise against surgery and propose standard treatment as a better alternative in this individualised approach. After counselling, the patient is asked for consent for surgery as is a standard preoperative requirement regardless of study participation. Participants in the intervention group may thus decide not to proceed with the surgical intervention. Participants who do not consent to surgery will continue the RCT in the intervention group, but receive treatment according to standard care. Patients receiving standard of care may be referred back to their own physician following the counselling.

When a participant and the MDT agree to surgery, an endoscopic transsphenoidal surgical resection of the prolactinoma is performed according to standard practice in an expertise centre. Patients are hospitalised for 2–5 days postoperatively. In the first weeks after discharge from the hospital, frequent contact by phone or visits to the outpatient clinic are needed to check for complications and recovery of the patient, according to the standards of care of the neurosurgical centre. The frequency of these visits is gradually reduced to (half-)yearly visits depending on the patient’s well-being.

#### Control: standard care

All participants who are randomised for standard care will receive treatment as usual from their own endocrinologist or gynaecologist as described by the US Endocrine Society [4].

First-line treatment is with DA, of which cabergoline is used most often; alternatives are bromocriptine and quinagolide. The dosage is usually titrated to achieve a normal or suppressed prolactin level in combination with restoration of the gonadal axis. DA treatment is discontinued after 2 years of treatment, i.e. 24 months after randomisation, unless a normal prolactin level cannot be achieved, and is restarted when prolactin levels rise after the medication is discontinued. As is customary in standard care, patients in the control group may be offered surgery in case of DA intolerance (side effects) or an insufficient response to DA treatment.

All participants may use any form of co-medication when medically indicated. Surgery is not performed on a pregnant participant, unless specifically indicated. Women who are pregnant at the time of randomisation are therefore not eligible for inclusion in an RCT. If a patient enrolled in one of the RCTs becomes pregnant after randomisation, she will remain in the trial, but treatment will be adapted, according to standard clinical care.

Our intervention protocol has been conceived in agreement with current standards of care for prolactinoma patients with an indication for surgery. Therefore, there are no specific strategies to improve adherence to intervention protocols. However, as part of the outcome data, we do monitor which treatment, surgical or medical, participants receive.

### Outcome assessment

Assessment of clinical outcomes takes place during outpatient clinic visits at 12, 27, 36, and 60 months after randomisation (PRolaCT-1, PRolaCT-2, and PRolaCT-3), or after study baseline (PRolaCT-O). For PRolaCT-O, study baseline is defined as the moment randomisation would have taken place, thus after all baseline measurements are performed and when treatment is chosen. An extensive overview of enrolment, interventions, and outcome assessment is given in Table 1. During these visits to the outpatient clinic, registration of prolactinoma treatment, physical symptoms, pregnancy, laboratory measurements (including prolactin level), and pituitary MRI (only at 12 and 36 months) takes place. For all surgically treated patients, the final registration of complications takes place during the outpatient clinic visit at 12 months. At every time point, assessment of patient-reported outcome measurements (PROMs) will take place using self-reported questionnaires. These questionnaires assess HRQoL and the presence and burden of physical and psychiatric symptoms or side effects to treatment. In all PRolaCT study arms, PROMs will additionally be collected every 3–6 months after randomisation/study baseline until *T* = 36 for a cost-effectiveness analysis.

**Table 1 Tab1:**
[figure not shown]
Overview of enrolment, interventions, and outcome assessment

^a^Measured 6, 9, 12, 18, 24, 27, 30, and 36 months after *T* = 0

^b^Measured every 6 months after *T* = 0

^c^Only in PRolaCT-O

### Primary outcomes

The two primary outcomes PRolaCT aims to evaluate are:
Health-related quality of life after 12 months of follow-upDisease remission after 36 months of follow-up

#### Health-related quality of life

The primary outcome measure HRQoL is defined as the score on the mental health scale (MHS) of the Medical Outcomes Study (MOS) Short-Form Health Survey (SF-36) after 12 months of follow-up, a time point reflecting a stable situation after surgical treatment or during DA treatment. The SF-36 is the most frequently used questionnaire in prolactinoma patients and has been validated in Dutch and English [22, 31]. The SF-36 is composed of 36 items, organised into eight multi-item scales, including the MHS. The seven other scales assess physical functioning, role limitations due to physical health problems, bodily pain, general health perceptions, vitality, social functioning, and role limitations due to emotional problems [31–33]. In addition to scoring on these scales, the SF-36 also yields two higher order component scores, one for physical health and one for mental health [31–33]. For our primary endpoint, only the score on the MHS will be used, and scores on the other scales and the two component scores will be used for secondary outcome measurements. The MHS score ranges from 0 to 100 and is known to be decreased in patients with active or treated prolactinomas [18–22].

#### Disease remission

Disease remission is defined as the presence of either normoprolactinaemia, which is defined as a prolactin level below the upper limit of normal for the respective laboratory, in the absence of DA treatment for at least 3 months; or pregnancy that was established during at least 3 months of withdrawal of DA treatment. The primary outcome assessment of disease remission is at 36 months of follow-up, reflecting remission after 2 years of DA treatment or long-term remission after surgery.

